#### Statistical analysis

The data collection and entry into the computer will be performed by the assessors using the method of double data entry. The collected data will be sent to the statistician without identifiers. The data will be analyzed using the SPSS 24.0. The principle of intention-to-treat analysis will be used with multiple imputations. Continuous data will be analyzed by means of the *t* test or Wilcoxon rank-sum test; categorical data will be analyzed using Fisher’s exact test or Wilcoxon rank-sum test.

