### Outcomes

#### Primary outcome

In the present study, the primary outcome will be the variation in the scores pertaining to the global scale of the Quality of Life Questionnaire for Functional Digestive Disorders (FDDQL) after 3 weeks. FDDQL is a questionnaire with forty-three items and eight subdomains (activities, anxiety, diet, sleep, discomfort, health perceptions, coping with disease, and impact of stress), used for the evaluation of the quality of life in patients with functional digestive disorders [18]. A validated Chinese version of the FDDQL will be adopted for the study (Cantonese in Hong Kong) [19, 20].

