### Statistical methods

#### Sample size

In our pilot observations, the global score of FDDQL pertaining to the patients who received BXD showed improvements with an effect size of 0.3–0.88. In the current study, the sample size was estimated with an average effect size of 0.6. The sample size required to achieve a statistical difference was estimated to be 22 patients per group (at *α* = 0.05, power = 80%, with a 95% confidence interval). Taking the dropout rate of 15% into consideration, a sample size of 84 patients (42 patients per group) is preferred. An interim analysis will be conducted to determine the adequacy of the sample size.

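### The primary FDDQL change is assigned to an unadjusted t test or Wilcoxon test, with the choice left open, although a baseline-adjusted analysis of the same data would be more precise and would pool directly over imputations

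*Protocol article*

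**What the plan says.** Under Primary outcome, the protocol article states that "the primary outcome will be the variation in the scores pertaining to the global scale" of the FDDQL after 3 weeks. Tables 1 and 2 schedule the FDDQL at day 0 and day 21 in both groups, so each patient is due to have a baseline score and a 3-week score.

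Under Statistical analysis, the method for every continuous outcome, the primary one included, is "Continuous data will be analyzed by means of the *t* test or Wilcoxon rank-sum test". No covariate is named and no rule selects between the two tests. The same paragraph says "The principle of intention-to-treat analysis will be used with multiple imputations" and "The data will be analyzed using the SPSS 24.0". It does not say which estimate is carried from each imputed dataset into the pooled result.

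Under Sample size, "the sample size was estimated with an average effect size of 0.6". The article does not say which standard deviation this effect is measured in.

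**The concern.** A change score subtracts the whole baseline value, so its baseline coefficient is fixed at 1. Regression estimates that coefficient from the data, which removes more noise unless the best coefficient happens to be 1. Power is not plentiful here: on the article's own effect size and dropout, the unadjusted two-sided comparison falls short of the 80% target.

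Two smaller points lie in the same sentence. Naming two tests for one primary endpoint leaves open which p value decides the trial. And a rank-sum p value is not itself an estimate with a standard error, which is what Rubin's rules combine, so the Wilcoxon option does not fit the stated imputation without a further choice.

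**Working it through.** **Inputs from the article.** Effect size 0.6, alpha 0.05, power 80%, 42 patients per group and 15% dropout (Sample size); change in FDDQL at 3 weeks (Primary outcome).

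**Assumptions.** The article does not give r, the correlation between baseline and day-21 FDDQL; I use 0.3 to 0.9. It gives no standard deviations; I take equal variances at the two times. I read 0.6 in SDs of change and test two-sided, because sidedness is not stated.

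**The plan's own figure.** The article says the need "was estimated to be 22 patients per group". For a two-group comparison, n = 2 × ((1.96 + 0.84)/0.6)² = 43.6, so 44 per group (45 with the t distribution). The figure of 22 appears only from the one-sample or paired formula, ((1.96 + 0.84)/0.6)² = 21.8. That mismatch is a separate issue; for this point the relevant sample is the planned 42 per group.

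**Unadjusted test.** Completers: 42 × 0.85 = 35.7, about 36 per arm. The noncentrality is 0.6 × √(36/2) = 2.55 on 70 degrees of freedom, giving power of 71% (72% by the normal approximation).

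**Variance ratio.** In units of the score variance:
- change score: 2(1 − r)
- ANCOVA: 1 − r²
- ratio: (1 − r²) / [2(1 − r)] = (1 + r)/2

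The effective effect size under ANCOVA is 0.6/√((1 + r)/2). At 36 per arm, ignoring the one degree of freedom spent on the covariate:

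| r | Variance ratio | Effective effect | Power |
|---|---|---|---|
| none (unadjusted) | 100% | 0.600 | 71% |
| 0.3 | 65% | 0.744 | 88% |
| 0.5 | 75% | 0.693 | 83% |
| 0.7 | 85% | 0.651 | 78% |
| 0.8 | 90% | 0.632 | 75% |
| 0.9 | 95% | 0.616 | 73% |

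At r = 0.6 the ratio is 0.80, so the need is 0.80 × 43.6 = 34.9, or 35 completers; 35/0.85 = 41.2, or 42 per arm. Up to about that correlation, adjustment alone reaches the stated 80% with the planned sample.

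**Unequal variances.** Let k be the follow-up SD divided by the baseline SD. In units of the baseline variance, the change-score variance is 1 + k² − 2rk and the ANCOVA variance is k²(1 − r²). The difference is (1 − rk)², which is never negative. The direction of the gain therefore does not depend on equal variances; its size does.

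**Open choice of test.** Simulated at 36 per arm under three data shapes (normal, heavy-tailed, skewed), the type I error is 6.0% to 6.8% if the smaller of the two p values is always taken. It is 4.8% to 5.1% if a normality pre-test decides.

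**Pooling a rank analysis.** The Mann-Whitney probability has an estimate and a standard error. Pooled by Rubin's rules over 10 imputations, with 42 per arm, 15% missing and r = 0.5, it gave a simulated type I error of 4.2%, and power of 72% at an effect of 0.6.

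**The case against.** Four stronger readings are tempting, and the article supports none of them.

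- **The baseline score is thrown away, or the comparison is biased.** It is not. A change score uses baseline with coefficient 1, and under 1:1 randomisation the comparison is unbiased with the right type I error. The loss is one of efficiency.
- **A change score always over-corrects when r is below 1.** The best coefficient is r times the ratio of follow-up to baseline SD, so this depends on SDs that the article does not give.
- **The Wilcoxon option makes the imputation analysis impossible.** The simulation above shows that a rank-based effect can be pooled. The fair statement is that no quantity to pool is named, and an analysis plan that is not shown may supply one.
- **The test will be picked after seeing the data.** The text is silent on selection. Silence is not evidence of a post hoc choice, and the inflation to 6.0% to 6.8% needs deliberate selection of the smaller p value.

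The size of the gain is also open to challenge, and this part stands. If 0.6 is in raw-score SDs, the effective effects are 0.6/√(2(1 − r)) unadjusted and 0.6/√(1 − r²) adjusted. Power at 36 per arm is then 56% against 75% (r = 0.3), 71% against 83% (r = 0.5) and 90% against 94% (r = 0.7). The pilot effect is described in patients who received BXD, so it may not be a between-group contrast at all. And 36 is a completer count, whereas the plan imputes for all 42; with 42 full observations the unadjusted power would be 78%, an upper bound because imputation does not restore lost information in full.

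That an analysis plan may exist does not remove the main point. The article states unadjusted tests; a plan that specified ANCOVA would depart from it.

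**Conclusion.** The point holds as one of efficiency and specification, not of validity. The stated primary analysis is one of two unadjusted tests, with the choice left open, where a baseline-adjusted model on data already scheduled would cut the variance by 5% to 35% for r from 0.9 to 0.3. Power at 36 completers per arm would rise from about 71% to between 73% and 88%. These sizes rest on an assumed r, equal variances and an effect of 0.6 in SDs of change, none of which the article states. That adjustment does not increase the variance, apart from one degree of freedom, holds without the equal-variance assumption.

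The lack of a named quantity to pool under the Wilcoxon option is a secondary gap, closed by the same change. This should be changed, but the trial would not be invalid without it.

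**What to change.** State one primary analysis: linear regression (ANCOVA) of the day-21 FDDQL global score on randomised group and baseline FDDQL global score, fitted in each imputed dataset, pooled by Rubin's rules, and reported as an adjusted mean difference with its 95% confidence interval. Use the same model, each with its own baseline, for HADS and EQ-5D-5L at day 21. Keep the Wilcoxon rank-sum test as a named sensitivity analysis.

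The cost is a change of wording. No visit, measurement or patient is added, and linear regression runs in the planned software. Because the Sample size section foresees an interim analysis, the change should be dated before anyone sees outcome data by group.

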**Methods/design:**

A randomized, waitlist-controlled trial will be conducted. A total of 84 patients with *Wei-Pi* syndrome will be randomized into the BXD or waitlist control group in a ratio of 1:1. The patients in the BXD group will receive the semi-individualized BXD on the basis of the syndrome differentiation in CM, for a duration of 3 weeks and will be under follow-up for further 3 weeks after the completion of therapy. Conversely, the patients in the waitlist control group will undergo the same intervention and follow-up after a 3-week waiting period. In the current study, the primary outcome will be the variation in the scores pertaining to the global scale of the Quality of Life Questionnaire for Functional Digestive Disorders after 3 weeks. The secondary outcomes include the variations in the scores pertaining to the Hospital Anxiety and Depression Scale and the EuroQoL 5-dimension 5-level Questionnaire and the results of the liver and kidney function tests.

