**Fig. 1 Fig1:**
[figure not shown]
Flow diagram of patient recruitment

**Table 1 Tab1:** Assessment timetable for the treatment group

	Telephone screening	Screening	Baseline (Wk 0)	Intervention			Follow-up	
				Wk 1–Wk 3			Wk 4	Wk 6
Visit number	0	1	2	3 (tel)	4 (tel)	5	6 (tel)	7
Day	− 28 to − 14	− 13 to − 7	0	7 ± 2	14 ± 2	21 ± 2	28 ± 2	42 ± 3
Screening information	✓	✓						
Informed consent		✓						
Review In/Ex criteria	✓	✓	✓	✓	✓	✓	✓	✓
Medical history	✓		✓					
Demographics			✓					
Blood test		✓					✓	
Primary outcome								
*FDDQL*			✓			✓		✓
Secondary outcomes								
*HADS*			✓			✓		✓
*EQ-5D-5L*			✓	✓	✓	✓	✓	✓
*Concomitant medications*	✓	✓	✓	✓	✓	✓	✓	✓
*Safety and tolerability*				✓	✓	✓		

*EQ-5D-5L* EuroQoL 5-dimension 5-level, *FDDQL* Quality of Life Questionnaire for Functional Digestive Disorders, *HADS* Hospital Anxiety and Depression Scale (HADS), *In/Ex* inclusion and exclusion, *Tel* telephone interview, *Wk* week

**Table 2 Tab2:** Assessment timetable for the waitlist group

	Telephone screening	Screening	Baseline (Wk0)	Waiting period			Intervention			Follow-up	
				Wk1	Wk2	Wk3	Wk4–Wk6			Wk 7	Wk 9
Visit number	0	1	2	3 (tel)	4 (tel)	5	6 (tel)	7 (tel)	8	9 (tel)	10
Day	− 28 to − 15	− 13 to − 7	0	7 ± 2	14 ± 2	21 ± 2	28 ± 2	35 ± 2	42 ± 2	49 ± 2	63 ± 3
Screening information	✓	✓									
Informed consent		✓									
Review In/Ex criteria	✓	✓	✓	✓	✓	✓	✓	✓	✓	✓	✓
Medical history	✓		✓								
Demographics			✓								
Blood test		✓								✓	
Primary outcome											
*FDDQL*			✓			✓			✓		✓
Secondary outcomes											
*HADS*			✓			✓			✓		✓
*EQ-5D-5L*			✓	✓	✓	✓	✓	✓	✓	✓	✓
*Concomitant medications*	✓	✓	✓	✓	✓	✓	✓	✓	✓	✓	✓
*Safety and tolerability*							✓	✓	✓		

*EQ-5D-5L* EuroQoL 5-dimension 5-level, *FDDQL* Quality of Life Questionnaire for Functional Digestive Disorders, *HADS* Hospital Anxiety and Depression Scale (HADS), *In/Ex* inclusion and exclusion, *Tel* telephone interview, *Wk* week

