#### Secondary outcomes

The timeline with reference to the evaluation of the secondary outcomes is shown in Tables 1 and 2.

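### EQ-5D-5L is measured three times in both arms before the waitlist group is treated, but the only stated method is an unadjusted one-value-per-patient test and no EQ-5D-5L contrast is named; one baseline-adjusted repeated-measures model would serve better.

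*Protocol article*

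**What the plan says.** The randomised comparison lasts three weeks, because "the patients in the waitlist control group will undergo the same intervention and follow-up after a 3-week waiting period" (Abstract, Methods/design). Within that period Table 1 ("Assessment timetable for the treatment group") and Table 2 ("Assessment timetable for the waitlist group") both schedule EQ-5D-5L at baseline and at days 7, 14 and 21. Days 7 and 14 are telephone contacts; day 21 is not marked as one. FDDQL and HADS are taken only at baseline and day 21 in the same period.

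The primary outcome has a fixed time point: "global scale of the Quality of Life Questionnaire for Functional Digestive Disorders (FDDQL) after 3 weeks". The secondary outcomes do not. The abstract says "The secondary outcomes include the variations in the scores pertaining to the Hospital Anxiety and Depression Scale and the EuroQoL 5-dimension 5-level Questionnaire", with no week attached, and the section on secondary outcomes says only: "The timeline with reference to the evaluation of the secondary outcomes is shown in Tables 1 and 2".

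The method, under Statistical analysis, is general: "Continuous data will be analyzed by means of the" *t* test or Wilcoxon rank-sum test. The same paragraph plans an intention-to-treat analysis with multiple imputation. It mentions no baseline covariate, repeated-measures model or summary over visits.

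**The concern.** The stated method and the schedule do not fit well for this one questionnaire. A *t* test or rank-sum test needs one number per patient. EQ-5D-5L supplies three randomised follow-up values plus a baseline, and the article does not say which value, or which combination, enters the test. The trial is open-label and EQ-5D-5L is reported by the patient, so a free choice among three weeks, made after the data are seen, would weaken any claim about generic health status. The stated test also leaves out the baseline as a covariate, although it is collected and costs nothing to use.

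**Working it through.** **Inputs.** From the article: three common post-baseline visits (Tables 1 and 2) and α = 0.05 (Sample size; sidedness not given, two-sided assumed). Not in the article: the correlation *r* between EQ-5D-5L scores at different visits, so a range is shown. The article gives no error rate or precision for EQ-5D-5L, so there is no figure of its own to reproduce.

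**1. Error rate if all three visits were tested.**
- Independent tests: 1 − 0.95³ = 0.143.
- Correlated tests, by simulation of three two-sided z tests (2,000,000 draws):

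| Correlation between tests | Equal correlation | AR(1) |
|---|---|---|
| 0.3 | 13.6% | – |
| 0.5 | 12.5% | 13.0% |
| 0.7 | 11.0% | 11.5% |
| 0.8 | 9.8% | 10.3% |
| 0.9 | 8.4% | – |

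- Change scores share a baseline. With equal correlation *r* and unit variance, each change has variance 1 + 1 − 2*r* = 2(1 − *r*). Two changes have covariance *r* − *r* − *r* + 1 = 1 − *r*. Their correlation is (1 − *r*) / [2(1 − *r*)] = 0.5 whatever *r* is, which gives 12.5%.

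**2. Precision of a day-21 comparison.** The factor is the per-patient variance entering the group contrast, in units of the single-visit variance.
- Change score, *t* test: 2(1 − *r*). At *r* = 0.6 this is 0.80.
- Baseline-adjusted day 21: 1 − *r*². At *r* = 0.6 this is 1 − 0.36 = 0.64.
- Ratio: (1 − *r*²) / [2(1 − *r*)] = (1 + *r*)/2. This is 0.65 at *r* = 0.3, 0.80 at 0.6 and 0.90 at 0.8.

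The reduction at *r* = 0.6 is therefore 20%, and it comes from the baseline. With complete data, days 7 and 14 add essentially nothing to a day-21 contrast from a model with unstructured covariance.

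**3. A different target, for comparison.** The baseline-adjusted mean of the three visits has factor (1 + 2*r*)/3 − *r*² = 0.733 − 0.36 = 0.37 at *r* = 0.6. That gain belongs to the three-week mean. It must not be credited to a day-21 test, and it brings little or no gain in power if the effect builds up over the three weeks.

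**The case against.** The strongest reply is that this is a condensed article. The time point and the handling of repeated measures for a secondary outcome are commonly left to the full protocol or the SAP, neither of which is shown. The sentence on continuous data is generic, and it does not contradict the tables. That stands: the absence of a named visit would not on its own be a finding.

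Several stronger readings are tempting, and the document does not support them.
- **That EQ-5D-5L will be tested three times at 0.05.** Nothing says so; α = 0.05 appears only in the sample-size paragraph.
- **That the choice is between three tests and throwing two visits away.** One *t* test on the mean, or the area under the curve, of the three visits would use them all and fit the stated wording.
- **That the days 7 and 14 answers of a patient who misses day 21 are lost.** Multiple imputation is planned and could draw on them, although the article does not say that it will.
- **That the weekly contacts are wasted effort.** They also cover eligibility review and medications in both arms, and safety in the BXD arm.
- **That EQ-5D-5L is the only outcome recorded repeatedly.** Concomitant medication is recorded at the same visits. EQ-5D-5L is the only *questionnaire* of which this is true.

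It can also be said that naming one visit or one summary for the stated test would remove the multiplicity just as well. It would, but the test would still not adjust for baseline.

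**Conclusion.** The point holds as a cheap improvement to the analysis of a secondary outcome. For EQ-5D-5L the article states an unadjusted test of one value per patient against a schedule of three randomised follow-up values, with no contrast named. A better method exists for data already being collected.

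The false-positive risk is conditional. It is about 8% to 14% only if all three visits are tested at two-sided 0.05, and 12.5% further assumes change scores and equal correlation. The precision gain, from 0.80 to 0.64, assumes *r* = 0.6 and a change-score *t* test as the comparator. It shrinks as *r* rises. A reader might infer that the main conclusion of the trial is at risk. It is not: FDDQL has a single randomised follow-up, at day 21, and its time point is fixed.

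**What to change.** Analyse EQ-5D-5L over days 7, 14 and 21 with one mixed model for repeated measures: baseline EQ-5D-5L, group, visit and group by visit, with unstructured covariance. Name BXD minus waitlist at day 21, which matches the primary time point, as the only EQ-5D-5L test. Report days 7 and 14 as estimates with 95% confidence intervals and make no separate claims from them. State whether the model is fitted to the observed values or within the planned multiple imputation; either can use days 7 and 14 when day 21 is missing.

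The cost is a few lines of text and slightly more programming, and the model runs in SPSS 24. No new data are needed and the primary analysis does not change. What is given up is a significance claim at day 7 or day 14.

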### Exclusion criteria

The patients will be excluded on the basis of the following criteria:
Pregnancy or patients planning conceptionAbnormal liver function; patients with more than two times the upper limit of the normal range of aspartate transaminase (AST) and alanine aminotransferase levels (ALT) [16]Abnormal kidney function with an estimated creatinine clearance below 80 mL/min [17]History of diagnosis of gastric structural abnormalities by means of endoscopy or history of gastrectomyGlucose-6-phosphate dehydrogenase deficiencyAlcohol or drug abuseConsumption of Chinese medicine within 1 month prior to the commencement of the studyUnable to read/understand and sign the informed consent document

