##### Liver and kidney function tests

The patients will undergo liver and kidney function tests before and after the completion of therapy using modified BXD, in order to ensure patient safety and to determine the adverse effects of modified BXD. The blood AST, ALT, and creatinine levels of the patients will be evaluated using an automated chemistry analyzer (Sysmex BX-3000, Japan) in the Chung Tai X-Ray & Medical Laboratory Limited, Hong Kong.

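### The mean and rank tests stated for AST, ALT and creatinine cannot support a group-level conclusion on organ safety; counts of abnormal results among treated patients would

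*Protocol article*

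**What the plan says.** The Abstract lists "the results of the liver and kidney function tests" among the secondary outcomes. The outcome section on liver and kidney function tests gives their purpose: "in order to ensure patient safety and to determine the adverse effects of modified BXD". It also names the quantities: "The blood AST, ALT, and creatinine levels of the patients will be evaluated using an automated chemistry analyzer".

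Under Statistical analysis, the rules go by type of data and name no outcome. For continuous variables: "Continuous data will be analyzed by means of the" t test or the Wilcoxon rank-sum test. For the rest: "categorical data will be analyzed using Fisher’s exact test or Wilcoxon rank-sum test". No post-treatment abnormality endpoint is named.

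The protocol does have limits for abnormal organ function, but only under Exclusion criteria: AST and ALT more than twice the upper limit of normal, and, for the kidney, "Abnormal kidney function with an estimated creatinine clearance below 80 mL/min".

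Each patient has two blood tests. The first is at screening. The second is in week 4 for the BXD arm (Table 1) and in week 7 for the waitlist arm (Table 2), in both cases the week after the three treatment weeks. The waitlist arm has no blood test at the end of its waiting period.

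**The concern.** Herb-related liver or kidney injury, if it occurs, would be expected as a large change in a few patients rather than a small shift in everyone. A rank test registers only that those few patients rank highest, however extreme their values. In a t test the same values raise the standard deviation along with the mean, so the statistic hardly moves. The stated tests therefore ask whether the whole group shifted, while the stated purpose is to find adverse effects.

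At stake is how the results are read. A non-significant p-value on a listed secondary outcome is easily reported as showing that liver and kidney function were unaffected, and these laboratory values are the protocol's only objective safety measure.

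**Working it through.** The protocol gives no rate, power or threshold for the laboratory outcomes, so there is no figure of its own to reproduce.

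**Inputs from the protocol.** 42 patients per arm and 15% dropout: 42 × 0.85 = 35.7, taken as 36 per arm and 72 in all. Alpha 0.05, taken as two-sided.

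**Assumptions, not in the protocol.** ALT upper limit 40 U/L, baseline 22 U/L, change from baseline normal with mean 0 and SD 10, and k injured patients raised to five times the limit, a rise of 5 × 40 − 22 = 178 U/L. The control arm is assumed untreated, which favours the plan.

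**Why the t test fails.** The expected mean difference is 178k/36. The variance in the affected arm is about 10² + 178² × k(36 − k)/(36 × 35). For k = 3:
- difference: 178 × 3/36 = 14.8
- SD in the affected arm: √(100 + 2,489.5) = 50.9
- standard error: √((2,589.5 + 100)/36) = 8.64
- t = 14.8/8.64 = 1.72, against a critical value of 1.99

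The same steps give t = 0.90 for k = 1 and 1.36 for k = 2.

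**Why the rank test fails.** If the k patients exceed every control, U rises by 18k above its null mean of 648, whatever the size of the rise. The null SD is √(36 × 36 × 73/12) = 88.8. For k = 3, z = 54/88.8 = 0.61, against 1.96.

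**Simulation under these assumptions (share of trials with p<0.05, repeated runs agreeing within about one percentage point).**

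| Injured patients of 36 | t test | Rank-sum |
|---|---|---|
| 1 | 0.7% | 5% |
| 2 | 3% | 6–7% |
| 3 | 15–16% | 7–8% |
| 4 | 55% | 11% |

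**A different model.** ALT log-normal with median 20 U/L, log-SD 0.3 or 0.5, within-patient log-SD 0.25, and 35 or 42 per arm. With one to three cases, rank-sum rejects in about 4% to 8% of trials. The t test rejects in about 2% to 20% at three times the limit and 0% to 10% at ten times. With four cases the t test reaches 32% to 46% and 63% to 80% respectively, while rank-sum stays at 9% to 11%. The blindness thus concerns a few cases; for the t test it lifts from about four upwards.

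**The comparison the trial actually has.** Both arms have taken the decoction by the second blood test. If it harms a fraction p of patients, the expected fraction is p in both arms and the expected between-arm difference is zero, however large p is. The table above is therefore a best case for the stated tests.

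**What counts would show (Clopper-Pearson, 72 treated patients).** 2/72 = 2.8%, 95% CI 0.3% to 9.7%. 0/72 has an upper limit of 5.0%.

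**Kidney.** Using Cockcroft-Gault as an assumed estimate, a 55-year-old woman of 50 kg with creatinine 55 µmol/L has (140 − 55) × 50 × 1.04/55 = 80.4 mL/min. At 75 µmol/L she has 58.9 mL/min, yet this moves the mean of 36 patients by only 20/36 = 0.6 µmol/L. At 56 µmol/L she has 78.9 mL/min, so a trivial change also crosses the limit. A count of crossings needs the size of the change beside it.

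**The case against.** The strongest reply is that Statistical analysis is a generic list by data type. It also provides Fisher's exact test, and the protocol already speaks of abnormal organ function, so a normal/abnormal analysis is not ruled out. Threshold counts and shift tables are commonly left to an analysis plan, which is not shown. This limits the point but does not remove it: the named quantities are continuous levels, the article states a rule for continuous data, and that rule does not suit this outcome's purpose.

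It is also fair that a threshold test would do little better. Fisher's test gives p = 0.055 for 5/42 against 0/42 and p = 0.026 for 6/42. The gain comes from a visible count with an interval, not from another test.

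Three stronger readings are tempting, and the documents do not support them:
- A reader might infer that harm would be reported as no effect. The protocol has patients with abnormal results referred to a doctor (Safety and risk management), adverse events recorded, and safety data reviewed by the monitoring committee (Oversight and monitoring). Only the group test is shown to be uninformative.
- A reader might infer that the exclusion criterion on clearance and the outcome section on creatinine contradict each other. The latter names what the analyser measures; clearance can be estimated from that creatinine after treatment as at entry.
- A reader might infer that waitlist patients who leave before treatment would receive imputed post-treatment laboratory values. The sentence "The principle of intention-to-treat analysis will be used with multiple imputations" does not say that it covers safety laboratory data.

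**Conclusion.** The point holds as one about the group-level safety conclusion. For one to three markedly affected patients in an arm of 36, the stated tests reach p<0.05 in about 1% to 16% of trials (t test) or 5% to 8% (rank-sum, near its 5% false-positive rate), even against an untreated control. These percentages rest on assumed ALT distributions, but two quite different models lead to the same conclusion. That the between-arm comparison sets treated against treated needs no such assumption; it follows from Tables 1 and 2. A non-significant p-value on these outcomes would be no evidence of organ safety. Detection and referral of individual patients is not in question.

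**What to change.** Add to Statistical analysis that the liver and kidney tests are analysed separately from efficacy:

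- **Population:** patients of both arms, pooled, who took at least one dose of BXD, using observed values.
- **Liver:** number and percentage with post-BXD AST or ALT above the multiple of the upper limit already in the exclusion criteria, with exact 95% CI.
- **Shift table:** before against after treatment, also showing estimated creatinine clearance against the exclusion limit, by the same estimate as at screening. Count patients who newly cross the limit and give the size of each change.
- **Mean changes:** description only, with no significance test used as evidence of safety.

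The entry limits serve here only as reporting thresholds; nothing about patient management changes. The cost is a few sentences. The laboratory values are already collected, and clearance must already be estimated for eligibility. The drawback is wide intervals and a more modest safety statement: with no case among 72, the most that can be said is that rates above 5.0% are unlikely.
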